# Septic shock: ECMO beyond ARDS? Introducing the Simon two-stage protocol when randomisation is considered unethical

**DOI:** 10.1186/s13049-020-0714-3

**Published:** 2020-03-17

One of the great disappointments during the past decades has been the failure to convert advances in our understanding of the biologic features of sepsis into new therapies. Although numerous multicenter, randomized controlled trials have been conducted in the last 30 years, no reduction of septic shock mortality was achieved [1] [2]. [3] Taking together available evidence suggests that no sepsis specific therapies are available until today, although a roadmap on the way to a specific septic shock therapy might be on the horizon [3] [4] including artificial intelligence [5]. [6].

Interestingly, in the Surviving Sepsis Campaign guidelines [7] ECMO (**E**xtra **C**orporal **M**embrane **O**xygenation) is not mentioned as a treatment option.

ECMO has been a standard treatment for cardiac and respiraory failure in neonates and children for decades, [8] in contrast to adults where the debate about the benefit of ECMO still is ongoing.

A systematic review and meta-analysis showed that the use of veno-arterial life support (ECLS) in cardiac arrest was associated with a higher survival (NNT [number needed to treat] 7.7) as well as a better neurological outcome, in the setting of cardiogenic shock there was a higher survival with ECLS compared with IABP (NNT 3) [9].

Since even the efficacy of venovenous extracorporal membrane oxygenation with severe respiratory distress syndrome (ARDS) has been disputed controversially until today a randomized controlled trial comparing vv-ECMO with conventional treatment was initiated with the results published recently (EOLIA trial) [10]. The main causes of ARDS were bacterial pneumonia in 45% and viral pneumonia in 18% of the patients, 78% of the patients had severe sepsis or septic shock. Primary end point was mortality at 60 days. No difference was found in the initial intention-to-treat analysis. However, 35 patients (28%) in the control group crossed over to ECMO. In fact, reanalysis including crossover patients as treatment failure and comparing death/crossover to ECMO of the control group vs death in the ECMO group showed a 23% lower mortality in the ECMO group (NNT 5).

In addition, Robert Bartlett in an editorial in CCM argued that the difference of the intention to treat vs treatment failure analysis results from 35 patients in the conventional care group who crossed over to the ECMO group as rescue treatment when conventional care was failing. Accordingly, the study had become a study of early versus late ECMO. Therefore, the EOLIA trial had shown that ECMO should be used promptly when high-risk criteria are met, rather than as late rescue therapy when death from ARDS or multiple organ failure is imminent [11].

What about the use of va-ECMO in the treatment of septic shock? To date, ECMO is suggested only as rescue therapy [12] and only observational case series with some promising results have been published (for overview see Table 1). However, the impression is not unequivocal. Thus, in a commentary discussing the results of Ro et al. the question is asked whether ECMO therapy in septic shock is a heroic futility or not [27]. The authors come to the conclusion that in this study more than half of the patients had liver cirrhosis, including post-liver transplantation and the patient cohort was derived from the years 2005 through 2012; both factors could adversely affect outcomes. On the contrary, the results of a just recently published observational study [26] are very promising with a hospitality mortality of just 10% in cytotoxic cardiac failure and 30% in distributive shock.

**Table 1 Tab1:** Observational studies using ECMO in adult septic shock, modified and extended according to Riera [13] et al.

Study	N	Sites of infection %	ECMO configuration	Hospital Survival %
Brechot et al. [14]	14	Pneumonia bacterial 79 Abdomen 14,3	Peripheral va 36% Switch to vv	71
Huang et al. [15]	52	Pneumonia 48 Abdomen 23 Urinary tract 9,6	Peripheral va	15
Cheng et al. [16]	108	Pneumonia bacterial 40 Myocarditis 25 Primary bloodstream 19,4	Peripheral va 78,7 Peripheral vv 21,3	28,7
Park et al. [17]	32	Pneumonia bacterial 34,4 Abdomen 21,9 Urinary tract 12,5	Peripheral va	21,9
Cheng et al. [18]	151	Pneumonia 50,3 Myocarditis 19,9 Bloodstream 14,6 Abdomen 7,6	Peripheral va 66,9 vv 33,1	29,8
Von Bahr et al. [19]	255	Pneumonia bacterial 53 Pneumonia viral 12,5	vv 68 switch to va peripheral 21 switch to vv 16	64
Takauji et al. [20]	40	Pneumonia 62,5 Abdomen 20 Urinary tract 7,5	vv	47,5
Yeo et al. [21]	8	Pneumonia *n* = 5 Extra-pulmonary *n* = 3	vva	50
Choi et al. [22]	28	Pulmonary 46,4 Abdomen 14,3 Genitourinary 7,1 Skin or soft tissue 14,3 Cardiovascular 7,1 Central nerve system 3,6 Catheter-induced 3,6 Other 3,6	vv, va, vva	35,7
Ro et al. [23]	71	Pneumonia 70 Abdomen 11 Urinary tract 5 Other 14	va	7
Vogel et al. [24]	12	Septic cardiomyopathy *n* = 12	vva	75
Banjas et al. [25]	19	Pneumonia 53 Abdomen 42 Soft tissue 5	vv, va, vva	42
Falk et al. [26]	37	Lung *n* = 21 Gut *n* = 2 Pyelonephritis *n* = 4 Fasciitis *n* = 4 Urine n = 1 Blood n = 4 Myocarditis n = 1	vv, va	Distributive shock 70,6 Cytotoxic Cardiac failure 90,0

In this situation where randomized controlled trials are considered unethical, Bartlett suggests that the matched pairs method is the best study design for evaluation of life support systems in acute fatal illness in a high risk population early [8].

For patients with septic shock we suggest another approach – the Simon [28] two-stage non-randomized method including only patients with septic shock (Sepsis-3 definition [7];) resulting from secondary peritonitis.

The Simon protocol is a Phase 2 design. According to Evrard et al. “Phase 2 is a completely underutilized tool in surgery that could raise the level of scientific reporting. The threshold for efficacy and nonefficacy is defined and with statistical power (risks *a* and *b*), the cohort size is calculated (usually, between 30 and 60 patients). The use of interim stopping rules allows reduction of the required number of patients (e.g., Simon design)” [29].

We use the following assumptions: ECMO treatment is considered as poor (P_0_) if mortality is above 55% and as sufficient (P_1_) if it is below 40% with a two-sided alpha of 0.05 and a beta of 0.20.

Inclusion criteria: Overcoming the criticism of sepsis trials in the past, namely heterogeneity of patient populations (ie mixing medical and surgical patients), we are only studying septic shock due to secondary peritonitis, a group with a reported very high mortality; age: 18–70 years, norepinephrine > 0,5 μg/kg/min despite adequate volume substitution (30 ml/kg) within the first 12 h, serum lactate > 2 mmol/l, duration of septic shock < 24 h (ie ECMO is initiated as an *early* and not as a rescue therapy); Exclusion criteria: Septic shock due to other sources than the abdomen, peripheral arterial occlusive disease excluding femoral/axillary vessel cannulation; duration of septic shock > 24 h; patient waiver concerning life support measures.

The ECMO route is peripheral with an initial flow ≥4.5 l/min and norepinephrine should be reduced at least to below norepinephrine > 0,5 μg/kg/min. The standard protocol in patients with VA-ECMO is to adjust the blood flow of the machine and the dosage of norepinephrine in order to achieve a mean arterial pressure of at least 65 mmHg. After achieving this MAP norepinephrine is tapered if possible, to below 0.1 μg/kg/min. In addition, inferior vena cava saturation is monitored continuously with a target saturation above 55. Finally, transthoracic echocardiography is performed daily when norepinephrine dosage is above 0.5 μg/kg/min.

CRRT will be used while on ECMO (default CRRT is SLED, it might be possible to use the oxygenator for connecting the dialysis machine, depending on the arterial and internal pressure of the oxygenator, if too high, a separate dialysis catheter has to be established). Distal arterial limb perfusion is used in every patient by a 6F sheat strengthened by wire. Filters for removing cytokines are not allowed.

The design with a moderate cluster effect results in the following study conditions: Include 40 patients at a first stage and reject the approach if 16 or less patients survive (and 24 more die).

Otherwise, the second stage will be recruited until overall *n* = 79 patients are included. The treatment approach will be rejected if overall 43 or less patients survive (i. e., 36 or more patients die).

This study design follows important recommendations: First, it is not a randomized trial (ie avoiding ethical issues, [30] [8]; and second, the defined patient population has a high mortality risk and avoids heterogeneity. Moreover, the Simon approach leads rapidly to results in a small number of patients in which a minimum of data collection could be provided [31].

In conclusion in answering the question ‘Septic shock – ECMO beyond ARDS?’ we strongly believe, against the background of quite discrepant results of observational studies (see Table 1 [13])that va-ECMO should be studied as outlined in the above protocol with emphasis on *early* ECMO (ie not as *rescue* ECMO) when failure of conventional therapy for septic shock is evident: norepinephrine > 0,5 μg/kg/min despite adequate volume substitution (30 ml/kg) within the first 12 h and serum lactate > 2 mmol/l*.*

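### The stated two-sided alpha of 0.05 does not match the printed Simon rule, which fits a one-sided 0.05: its exact false-positive rate is 0.036 against 0.025 per tail

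*Protocol article*

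**What the plan says.** The statistical assumptions are in the unnumbered main text of the protocol article. The null is a mortality of 55%: "ECMO treatment is considered as poor (P_0_) if mortality is above 55" per cent. The alternative is a mortality of 40%: "as sufficient (P_1_) if it is below 40" per cent. The error rates follow: "with a two-sided alpha of 0.05 and a beta of 0.20". The method is "the Simon [28] two-stage non-randomized method".

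The decision rule comes later in the main text, introduced by "The design with a moderate cluster effect results in the following study conditions". Stage 1: "Include 40 patients at a first stage and reject the approach if 16 or less patients survive". Stage 2: "the second stage will be recruited until overall *n* = 79 patients are included". Final rule: "The treatment approach will be rejected if overall 43 or less patients survive (i. e., 36 or more patients die").

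No intracluster correlation, cluster size or design effect is given.

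**The concern.** Both printed boundaries lead to rejection. The approach can be accepted only at the end of stage 2, with 44 or more survivors of 79, so the rule has one kind of false positive: accepting ECMO when survival is really 45%. A two-sided alpha of 0.05 conventionally leaves 0.025 for that error, whereas a one-sided alpha leaves 0.05. The two statements ask for different cut-offs or different sample sizes, so the stated error rates and the printed rule should be checked against each other.

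The trial has no control arm, so the error rates of this rule are the main statistical protection against a mistaken go decision. The two readings also differ at a result that could occur: 44 survivors of 79 passes the printed rule but fails a rule held to 0.025 per tail.

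**Working it through.** **Inputs (all from the article's main text).** Survival p0 = 1 − 0.55 = 0.45 and p1 = 1 − 0.40 = 0.60. Stage 1: n1 = 40, stop at r1 = 16 or fewer. Total N = 79, so stage 2 adds 79 − 40 = 39 patients. Final cut-off r = 43, so success needs 44 or more. Outcomes are treated as independent at first, because the article gives no figure for clustering.

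**1. Operating characteristics of the printed rule.**

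P(accept | p) = Σ over x = 17 to 40 of Bin(x; 40, p) × P[Bin(39, p) > 43 − x]

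- At p = 0.45: 0.0363. The probability of stopping after stage 1 is 0.319.
- At p = 0.60: 0.8146, so beta is 0.185.

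The stated beta of 0.20 is met. The false-positive rate is below 0.05 but above 0.025, by 0.0363 − 0.025 = 0.0113, or 1.1 percentage points. Ignoring the interim look changes little (0.0364 and 0.8152).

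**2. Which alpha does the cut-off fit?** First stage held at 16/40, N = 79:

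| Reject at or below | P(accept at 45%) | P(accept at 60%) |
|---|---|---|
| 42 | 0.0581 | 0.8684 |
| 43 (printed) | 0.0363 | 0.8146 |
| 44 | 0.0217 | 0.7483 |

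The printed 43 is the lowest cut-off that holds 0.05 in the upper direction. To hold 0.025, the cut-off must be 44, and power then falls to 0.748 (beta 0.25).

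**3. Can any design with N = 79 meet 0.025 and 80% power?** A search over every n1, r1 and r at N = 79 finds none. The highest power with a false-positive rate of at most 0.025 is 0.7485 (alpha 0.0217). The smallest N that works is 89 (25/55, then 49/89: alpha 0.0222, power 0.8002). At a one-sided 0.05, by contrast, the minimax design needs only N = 70 (19/42, 38/70) and the optimal design N = 77 (12/26, 41/77), so 79 is ample. The printed design is neither of these.

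**4. Does the cluster effect change this?** The values below are assumptions. Variance inflation is a normal-approximation calculation; the intracluster correlation (ICC) rows simulate centres of about 10 patients. All use the printed rule.

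| Assumed clustering | P(accept at 45%) | Power at 60% |
|---|---|---|
| Variance inflation 1.1 | 0.043 | 0.80 |
| Variance inflation 1.2 | 0.050 | 0.79 |
| ICC 0.01 | 0.042 | 0.80 |
| ICC 0.02 | 0.049 | 0.795 |
| ICC 0.05 | 0.067 | 0.77 |

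Positive clustering widens the distribution of survivors. The cut-off lies above the null expectation (79 × 0.45 = 35.6), so the upper tail grows. Clustering therefore moves the rate further from 0.025.

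The cut-off of 44 suffers in the same way: with centres of about 10, its false-positive rate is about 0.027 at ICC 0.01, 0.031 to 0.032 at 0.02 and 0.047 to 0.048 at 0.05.

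**The case against.** The strongest reply is that the rule is sound and one word is wrong. The article does not say that 0.05 is split into 0.025 per tail; a Simon rule has a single success direction; and 0.036 is below 0.05. With this first stage, 43 is exactly the cut-off that a one-sided 0.05 would select, and power exceeds 80%. This stands. It identifies the likely source of the mismatch, and it means that neither the boundaries nor the number of patients needs to change. It does not remove the need to correct the sentence, because under the usual meaning of two-sided the stated property is not met.

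A second reply is that the boundaries were derived with a cluster effect, so figures under independence are not the design's own operating characteristics. This also stands as a limit on 0.036 and 0.815. It does not rescue 0.025, because positive clustering works in the opposite direction. With mild clustering the printed rule comes out close to 0.05 and 0.80, which again points to a one-sided alpha.

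A reader might go further and infer that the rule is too liberal, or that the trial would accept ECMO while its own 95% confidence interval still covers 45% survival. The documents do not support either. The rule complies with a one-sided 0.05 under independence. The article describes a count-based decision and no confidence interval. The fixed-sample exact 95% interval at 44/79 (44.1% to 66.9%) does include 45%, but it only restates the p-value from step 1 and ignores the two stages.

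**Conclusion.** The mismatch is confirmed. A two-sided alpha of 0.05 read as 0.025 per tail, a beta of 0.20 and N = 79 cannot all hold. The printed rule has a false-positive rate of 0.036 and power of 0.815, and so behaves as a one-sided 0.05 design.

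In absolute terms the excess over 0.025 is small, and the most plausible defect is the word describing sidedness, not the rule itself. It still needs correcting, because it misstates a main design property and leaves the reading of a 44/79 result open.

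The conclusion rests on the conventional meaning of two-sided and, for the exact figures, on independent outcomes. Positive clustering of any size leaves the mismatch in place and enlarges it. Beyond a variance inflation of about 1.2, even the one-sided 0.05 would be exceeded, so the unstated cluster assumption matters to the correction as well.

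**What to change.** **Preferred.** Replace the two-sided alpha with a one-sided alpha of 0.05. State the achieved false-positive rate and power under independence (0.036 and 0.81), and beside them the same two figures under the intracluster correlation or design effect that was assumed, with that value printed. If an interval is reported, make it a 90% two-sided one, which corresponds to a one-sided 0.05. The fixed-sample exact 90% lower limit at 44/79 is 45.8%, which excludes 45%. The boundaries and the number of patients stay as they are. The cost is a sentence or two and a less favourable stated alpha.

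**If two-sided 0.05 is kept.** Change the final rule to reject at 44 or fewer survivors (79 − 44 = 35 or more deaths), and restate power as about 75% with a false-positive rate of 0.022, noting that both figures hold only without clustering. This adds no patients but gives up the stated beta of 0.20. Keeping both two-sided 0.05 and 80% power would need at least 89 patients before any allowance for clustering.

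The choice should be recorded before the stage 2 result is known, because 44 survivors passes under the first option and fails under the second.

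### The printed two-stage rule does not deliver two-sided alpha 0.05 and beta 0.20 with a moderate cluster effect: it misses 0.025 without clustering, and has one-sided slack only to a design effect of about 1.13

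*Protocol article*

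**What the plan says.** The article proposes "the Simon [28] two-stage non-randomized method including only patients with septic shock" from secondary peritonitis. Its paragraph of statistical assumptions, just before the inclusion criteria, sets the two hypotheses: "ECMO treatment is considered as poor (P_0_) if mortality is above 55" per cent, and "as sufficient (P_1_) if it is below 40" per cent, "with a two-sided alpha of 0.05 and a beta of 0.20".

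The boundaries come later, after the description of ECMO and renal replacement. They are introduced by "The design with a moderate cluster effect results in the following study conditions". Stage 1 is "Include 40 patients at a first stage and reject the approach if 16 or less patients survive". Otherwise "the second stage will be recruited until overall *n* = 79 patients are included", and "The treatment approach will be rejected if overall 43 or less patients survive".

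The cluster effect is thus presented as part of what produced the boundaries. The article gives no cluster unit, number of clusters, ICC or design effect.

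**The concern.** Correlation between patients in the same cluster widens the distribution of the survivor count. With a fixed count threshold, a poor treatment then passes more often and a good one is missed more often than under independence. A rule said to hold its error rates under moderate clustering should therefore have visible slack when patients are independent. Here the slack is small on a one-sided reading of alpha and absent on the two-sided reading that the article states.

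At stake is how a positive result would be read. The trial has a single arm and the decision rests on one count, so the stated alpha is the reader's only measure of how easily a treatment with 55% mortality could be declared worth pursuing.

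**Working it through.** **Inputs, all from the article.** Survival under the poor hypothesis p0 = 1 − 0.55 = 0.45; under the sufficient hypothesis p1 = 1 − 0.40 = 0.60. n1 = 40, r1 = 16, n = 79, r = 43, so stage 2 has 39 patients and success needs at least 17 survivors of 40 and at least 44 of 79.

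**Step 1: independent patients, exact.**

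P(success | p) = Σ over x = 17 to 40 of P(X1 = x) × P(X2 ≥ 44 − x), with X1 ~ Bin(40, p) and X2 ~ Bin(39, p).

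- p = 0.45: type I error 0.0363 (early-stop probability 0.319).
- p = 0.60: power 0.8146.

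The power claim of 80% is reproduced, with 1.5 points to spare. The type I error is below 0.05 but above 0.05/2 = 0.025, which a two-sided 0.05 allows in the efficacy direction. Moving only the final boundary to 44 gives type I error 0.0217 but power 0.748, so 79 patients with this first stage do not meet 0.025 and 80% together.

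**Step 2: ordinary Simon designs for comparison.** These come from an exhaustive search under independence.

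| One-sided alpha | Optimal (r1/n1, r/n) | Minimax (r1/n1, r/n) |
|---|---|---|
| 0.05 | 12/26, 41/77 | 19/42, 38/70 |
| 0.025 | 17/34, 58/109 | 25/55, 49/89 |

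None is 16/40, 43/79. At 0.025 even the smallest total is 89.

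**Step 3: how much clustering the rule can absorb on a one-sided 5%.** A normal approximation to the final count, with variance multiplied by a design effect (DE), gives:

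- Under p0: mean 79 × 0.45 = 35.55, SD √(79 × 0.45 × 0.55) = 4.42. Alpha reaches 0.05 at DE = [(43.5 − 35.55)/(4.42 × 1.645)]² = 1.19.
- Under p1: mean 79 × 0.60 = 47.4, SD √(79 × 0.60 × 0.40) = 4.354. Power falls to 0.80 at DE = [(47.4 − 43.5)/(4.354 × 0.8416)]² = 1.13.

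A beta-binomial search over 3 to 20 centres puts the limits at DE 1.18 to 1.19 (alpha) and 1.13 to 1.14 (power).

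**Step 4: what that means in ICC terms.** The following are assumptions, not figures from the article: the clusters are centres, K of them, as equal as possible in both stages, with beta-binomial survival. DE = 1 + (79/K − 1) × ICC. The values below are exact sums under that model; simulation with 200,000 or more runs agrees to within about 0.002.

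| K | ICC | DE | Alpha | Power |
|---|---|---|---|---|
| 40 | 0.10 | 1.10 | 0.0436 | 0.8037 |
| 10 | 0.01 | 1.07 | 0.0414 | 0.8067 |
| 10 | 0.02 | 1.14 | 0.0464 | 0.7994 |
| 20 | 0.05 | 1.15 | 0.0471 | 0.7985 |
| 5 | 0.02 | 1.30 | 0.0578 | 0.7844 |
| 10 | 0.05 | 1.34 | 0.0613 | 0.7803 |
| 10 | 0.10 | 1.69 | 0.0846 | 0.7553 |
| 5 | 0.05 | 1.74 | 0.0877 | 0.7522 |
| 5 | 0.10 | 2.48 | 0.1289 | 0.7170 |

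The first four rows hold or hold to within 0.2 of a power point; in the last five both one-sided rates fail.

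**The case against.** The strongest objection is that the deciding inputs are not in the article. It does not say that clusters are centres, how many there are, or how large the ICC is, so the failing rows in the table rest on assumptions. That stands. A reader might infer that any real centre effect breaks both error rates; the documents do not support this. Many small clusters or a low ICC leave the rule intact or nearly so, and between a design effect of about 1.13 and 1.18 only power fails, by less than a point.

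A reader might also infer that no cluster allowance was made and that the phrase is simply false. That cannot be shown either. The total of 79 exceeds the one-sided minimax total of 70 by a factor of 79/70 = 1.13, which matches the power limit, although it is only 2 above the optimal total of 77. A small allowance cannot be excluded. Nor does a survivor-count threshold prove that independence was assumed, since such a threshold can be derived under a correlated model.

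Third, a short article may leave the ICC and cluster count to the full protocol. This is fair, and their absence is not the point here. The article does print both the boundaries and the error rates, so that pairing can be tested.

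Finally, the gap between 0.036 and 0.025 concerns sidedness and exists with no clustering at all. That is correct, and it should not be attributed to clustering. It remains part of the same stated combination.

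**Conclusion.** The point holds in a limited form. The article presents 16/40, 43/79 as giving two-sided alpha 0.05 and beta 0.20 with a moderate cluster effect, and the rule does not deliver that combination. On the literal two-sided reading it fails under independence: 0.036 against 0.025. This needs no assumption beyond the article's own figures and the usual halving of a two-sided alpha.

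On a one-sided 5% reading it is sound under independence and tolerates a design effect of about 1.13 for power and 1.18 for alpha. Beyond that the size depends on unstated inputs. With equal centres and a beta-binomial model, the failing cases run from slight (10 centres, ICC 0.05) to substantial (5 centres, ICC 0.05, where alpha is 0.0877/0.0363 = 2.4 times the independence value). It is a correction to the stated operating characteristics and does not show that the design is unusable.

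**What to change.** Keep the boundaries and replace the stated alpha and beta with the one-sided alpha and power that 16/40, 43/79 has under the cluster assumption actually used, naming that assumption beside the figures. For example, if it was 10 equal centres with ICC 0.05, the text would read one-sided alpha 0.06 and power 0.78. If no allowance was made, delete the reference to a cluster effect and state one-sided alpha 0.036 and power 0.815 for independent patients. In either case, drop the description of alpha as two-sided.

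The cost is one recalculation and one sentence. The downside is that the stated error rates become less favourable. No extra patients are needed.

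### Rejection is tested only at 40 and 79 patients, although the 24th death in stage 1 or the 36th overall already settles it; closing recruitment there is a cheap improvement

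*Protocol article*

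**What the plan says.** The main text of the protocol article sets the thresholds as mortality: the treatment is poor "if mortality is above 55" percent and sufficient "if it is below 40" percent, "with a two-sided alpha of 0.05 and a beta of 0.20". In survival terms, P0 is 45% and P1 is 60%.

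The study conditions come later in the same text, introduced by "The design with a moderate cluster effect results in the following study conditions". For stage 1: "Include 40 patients at a first stage and reject the approach if 16 or less patients survive (and 24 more die". I read the death count there as 24 or more, which is what 16 or fewer survivors of 40 implies. If that boundary is not met, "the second stage will be recruited until overall" 79 patients are included. At the end: "The treatment approach will be rejected if overall 43 or less patients survive (i. e., 36 or more patients die".

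Both boundaries are therefore given as survivors and as deaths, and each is tied to a completed stage. The article has no rule for closing recruitment within a stage. Elsewhere it cites a smaller number of patients as the benefit of interim stopping rules.

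**The concern.** A death count can settle the result before the stage is full. After the 24th death among the first 40 patients, or the 36th death overall, no later outcome can prevent rejection. Under the article's text, recruitment still continues to 40 or 79.

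Patients enrolled after that point would receive peripheral va-ECMO, an invasive treatment, in a trial whose answer is fixed. They could sharpen the survival estimate and add safety information, but they could not alter the decision. The article presents its design as one that reaches a result quickly with few patients, so a rule that trims enrolment without touching the error rates serves its own aim.

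**Working it through.** **Inputs (protocol article, main text).** P0 survival = 1 − 0.55 = 0.45. P1 survival = 1 − 0.40 = 0.60. Stage 1: n1 = 40, reject at 16 or fewer survivors. Final: n = 79, reject at 43 or fewer survivors. Beta = 0.20. A cluster effect is named but not quantified, so every expected enrolment below assumes independent patients.

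**1. Reproduce the article's own figures.**
- Deaths at the boundaries: 40 − 16 = 24 and 79 − 43 = 36. Both agree with the text.
- Probability of rejecting at stage 1 under P0: P(X ≤ 16 | 40, 0.45) = 0.3185.
- Probability of accepting the treatment at survival p: the sum over x = 17 to 40 of b(x; 40, p) × P(Y ≥ 44 − x | 39, p). This gives 0.8146 at p = 0.60, consistent with the stated beta of 0.20, and 0.0363 at p = 0.45.

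**2. When is rejection certain?**
- With 24 deaths among the first 40, at most 40 − 24 = 16 can survive, so the stage 1 boundary is met.
- With 36 deaths overall, at most 79 − 36 = 43 can survive, so the final boundary is met.
- Both are counting arguments. They hold for any survival rate and any correlation between patients. As a check, 100,000 simulated trials gave no differing decision between stopping at these deaths and running to full size. Type I error therefore stays at 0.0363 and power at 0.8146.
- Earliest possible certainty: patient 24 in stage 1. In stage 2, at most 23 of the first 40 have died, so 36 − 23 = 13 more deaths are needed: patient 40 + 13 = 53.

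**3. Expected enrolment at P0, no reporting lag.**
- As written: 40 × 0.3185 + 79 × (1 − 0.3185) = 12.74 + 53.84 = 66.6.
- With stopping, an exact recursion over the running death count gives three outcomes: stage 1 rejection (probability 0.3185), known on average at patient 37.2; stage 2 rejection (0.6451), known on average at patient 67.6; acceptance (0.0363), at 79.
- Expected N = 0.3185 × 37.2 + 0.6451 × 67.6 + 0.0363 × 79 = 11.85 + 43.6 + 2.87, or 58.4 before the inputs are rounded.
- Saving: 66.6 − 58.4 = 8.2 patients overall. It is 40 − 37.2 = 2.8 in a stage 1 rejection and 79 − 67.6 = 11.4 in a stage 2 rejection.

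**4. Allow for reporting lag.** The article gives neither an accrual rate nor the time point for mortality, so the lag is an assumption. Let L further patients enrol before the deciding death is known, capped at the stage size:

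| L (assumed) | Mean N at P0 | Saving against 66.6 |
|---|---|---|
| 0 | 58.4 | 8.2 |
| 2 | about 60 | about 6.5 |
| 5 | about 62 | about 4.4 |
| 10 | about 65 | about 1.9 |

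**5. If the treatment works.** At 60% survival with no lag, mean N falls from 78.7 to 77.9, a saving of 0.8 patients. Any lag makes it smaller.

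**6. Effect on the estimate.** At P0 the mean of the naive survival proportion moves from 0.436 to about 0.433, because a stopped trial always ends on a death.

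**The case against.** The strongest reply is that nothing is wrong. The article chose the Simon two-stage design, which looks only at the end of each stage, and states its boundaries correctly and consistently in survivors and deaths. A full protocol or monitoring plan, not shown, may already close recruitment in practice once a boundary is reached. This stands to the extent that the point is an improvement and not an error, and that it concerns the article's text only. It does not remove the point, because the article itself fixes when stage 2 recruitment ends.

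The second reply is that the saving depends on knowing each death before the next patient enrols. A named cluster effect suggests several sites, where enrolment can overlap. This stands fully, and is why the saving is a range. Clustering would also change the mean saving, though not any decision.

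Two stronger readings are tempting, and the documents support neither.
- A reader might infer lives saved, since deaths among enrolled patients fall in step with enrolment (0.55 × 66.6 = 36.6 against 0.55 × 58.4 = 32.1). That only counts fewer patients. Those not enrolled still have septic shock from secondary peritonitis, there is no control arm, and P0 is a threshold for rejection, not evidence of harm.
- A reader might infer a much larger saving from the three series in Table 1 listed as va only (52, 32 and 71 patients; 15%, 21.9% and 7% survival). They pool to about (8 + 7 + 5)/155 = 13%. At 15% survival, stage 1 would stop near patient 28. But abdominal infection made up only 11% to 23% of those series, whereas this trial takes only secondary peritonitis and starts ECMO early. The article itself gives reasons why the 71-patient series may have done badly. A 14-patient series on peripheral va-ECMO, 36% of whom switched to vv, had 71% survival. The 15% case is an extreme scenario, not a forecast.

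Finally, fewer treated patients means slightly less precision and less safety information in a negative trial. That stands as a small cost.

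**Conclusion.** The point holds as a cheap improvement worth adopting. The article tests for rejection only at 40 and 79 patients, although the 24th death among the first 40 or the 36th overall decides the matter. That closing recruitment there leaves every decision, the type I error and the power unchanged is a certainty by counting and needs no model.

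The size does need a model. With independent patients and true survival at P0, the mean saving is about 2 to 8 patients over an assumed lag of 10 down to 0 further enrolments. Most of it comes from trials that fail in stage 2. If survival is 60%, almost nothing is gained. The documents do not support calling the design miscalculated, or claiming that the rule prevents deaths.

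**What to change.** Add to the study conditions: *Recruitment stops and the approach is rejected as soon as the 24th death among the first 40 patients, or the 36th death overall, is known.* Define a counted death as one that meets the trial's mortality endpoint. The rule closes recruitment only and leaves the care of enrolled patients untouched.

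Report the final survival estimate with an interval that allows for this stopping.

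The cost is one sentence, a running count of an outcome the trial records anyway, and prompt reporting of deaths. In negative trials the estimate is slightly less precise and its naive value very slightly lower. No boundary, stage size or power calculation changes. If the saving is quoted in the protocol, give it in patients enrolled, with the lag assumption beside it.
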